## Abstract

**Introduction:**

While myeloma is an incurable malignancy, developments in disease management have led to increased life expectancy in recent years. Treatment typically involves stem-cell transplantation. Increased survival rates equate to more patients living with the burden of both the disease and its treatment for increasing number of years, rendering myeloma a long-term condition.

Evidence exists to demonstrate the benefits of exercise for patients recovering from stem-cell transplantation, and prehabilitation—exercise before treatment—has been shown to be effective in other disease areas. To date there has been no research into prehabilitation in patients with myeloma awaiting transplantation treatment.

Our objective is to determine whether it is feasible to conduct a randomised controlled trial into pretransplant exercise for patients with multiple myeloma who are awaiting autologous stem-cell transplantation.

**Methods and analysis:**

This mixed methods study identifies patients with diagnosis of multiple myeloma who have been assigned to the autologous transplantation list and invites them to participate in six weekly sessions of individualised, supervised exercise while awaiting transplantation.

Quantitative data to determine feasibility targets include rates of recruitment, adherence and adverse events, and outcome measures including 6 min walking distance test and quality of life.

Qualitative interviews are undertaken with a purposive sample of patients to capture their experiences of the study and the intervention.

**Ethics and dissemination:**

Ethics committee approval has been obtained. Dissemination will be through open-access publications and presentations and will seek to reach multiprofessional bases as well as patients and carer groups, addressing the widespread interest in this area of research.

**Trial registration number:**

NCT03135925; Pre-results.

Strengths and limitations of this studyThe sample size for the qualitative aspect of this study is likely to be small—it is intended to inform future study design rather than provide definitive understanding.For practical reasons and to encourage patient recruitment, time points for data collection are aligned with clinical interventions, rather than specifically for research purposes. They are therefore subject to variations, and not within the control of the study team.As a feasibility study, this will not provide evidence of the effectiveness of prehabilitation, but will inform future study design for evaluating effectiveness.

## Introduction

Myeloma is an incurable malignancy of antibody producing B lymphocytes and plasma cells. Equating to seven new cases per 100 000 population in the UK, it represents 10% of all new haematological cancers.^1^ Disease symptoms include anaemia and hypercalcaemia causing fatigue and weakness, immunosuppression and lytic lesions of bone increasing pathological fracture risk.^2^

Due to developments in disease management, life expectancy has increased significantly in the last 10 years.^3^ The 5-year relative survival rate for England was 42.2% in 2011,^4^ and is set to increase further due to earlier interventions in the disease process, more effective chemotherapies and increased use of autologous stem-cell transplantation.^5^

Following diagnosis of multiple myeloma, the standard treatment for younger patients (generally, but not exclusively, under the age of 70) with adequate fitness consists of an intensive pathway starting with induction treatment using a variety of regimens delivered as an outpatient or day case given to control disease until maximum response is achieved (usually reflected by a plateau in serum paraprotein).^6–8^ This response is then consolidated with autologous stem-cell transplantation, which permits the administration of high-dose myeloablative melphalan chemotherapy, a procedure typically requiring around 3 weeks inpatient care, after which patients take several months to make a functional recovery.^6–8^ The procedure is non-curative and relapse/progression of myeloma occurs after an average of 2–3 years, which requires reinstitution of induction treatment, and, in many patients, consolidation with a second autologous transplant procedure.^9 10^

### Rationale for the study

Increased survival rates equate to more patients living with the burden of both the disease and its treatment for increasing number of years, rendering myeloma a long-term condition.^11^ The cumulative effects of the disease, compounded with the debilitating toxic nature of the treatment, impact significantly the quality of life of patients beyond the end of treatment, with late-effects symptoms including infection, fatigue, metabolic, neurological and cardiovascular disorders, as well as pain, physical fitness and psychological concerns.^12^

Only 20% of patients with myeloma meet national physical activity guidelines post-treatment,^12^and activity declines through treatment due to perceived barriers to exercise including pain, fear of injury and fatigue.^13^ Although research evidence in physical activity has been demonstrated to be limited,^14^ evidence exists to demonstrate the benefits of exercise for patients recovering from stem-cell transplantation.^15^ Prehabilitation after treatment in patients with myeloma has been shown to improve symptoms of physical performance, muscle strength, aerobic capacity, psychological outcomes, immunological function and fatigue.^16^ Exercise training for myeloma survivors has been shown to be safe and feasible during treatment with high attendance and adherence^17^ and has been implemented widely in clinical practice.

Studies demonstrate that pretransplant patients have reduced exercise capacity and increased comorbidities compared with a normal population, yet most rehabilitative interventions occur during and after treatment.^15^ Thus, while exercise rehabilitation after treatment for myeloma can be effective, we must also consider rehabilitative interventions prior to the start of treatment: prehabilitation, defined as,

a process on the continuum of care that occurs between the time of cancer diagnosis and the beginning of acute treatment … provides targeted interventions that improve a patient’s health to reduce the incidence and the severity of current and future impairments.^18^

Examples of prehabilitation exist in other clinical specialties: it has been used for some time in orthopaedic surgery to improve outcomes and postoperative recovery,^19^ and its economic benefits have been demonstrated within colorectal surgery.^20^ A review of prehabilitation in patients with presurgical cancer demonstrated the effective use of aerobic interventions in the management of patients undergoing thoracic surgery for lung cancer, identified the potential for its use in other oncology settings and called for further research to evaluate prehabilitation for wider groups of patients with cancer.^19^

Guidelines for the management of late and long-term effects of myeloma recommend that regular physical activity, including prehabilitation and rehabilitation, and aspiration to a general healthy lifestyle, are integral to patient care pathways.^12^

Autologous stem-cell transplantation has become the most common treatment in myeloma, with, for example, over 1400 performed in the UK annually, and procedures are performed in what is normally considered an elderly patient population, many with comorbidities and frailty. It is an intensive toxic procedure, with a recovery period of at least 6 months and strategies to improve recovery are warranted, including prehabilitation. A window of opportunity—usually a period of 4–6 months exists to offer prehabilitation between diagnosis or relapse and the commencement of the autologous stem-cell transplantation process. Coleman *et al*^21^ studied 24 patients with multiple myeloma undergoing a home-based exercise programme during chemotherapy and stem-cell transplantation and identified that no patient injured themselves and that the intervention had positive effects on lean body weight, fatigue and sleep disturbance. Despite this, no evidence currently exists regarding the use of prehabilitation exercise interventions in multiple myeloma.

This article describes the protocol for a study under way investigating the feasibility of research into the provision of an exercise intervention in patients with myeloma who are due to receive autologous stem-cell transplantation.

## Aims and objectives

The aim of this study is to determine whether it is feasible to conduct a randomised controlled trial into pretransplant exercise for patients with multiple myeloma who are awaiting autologous stem-cell transplantation.

We will determine this through completion of the following objectives:Assess the acceptability of the study to patients by measuring recruitment and retention to the study and through qualitative interview responses.Explore reasons for non-consent to study participation.Establish whether a target cohort of patients exists.Determine the most appropriate recruitment points postdiagnosis through steering group feedback, recruitment rate when compared with numbers invited to join the study and qualitative interview reports.Assess the suitability of inclusion and exclusion criteria by examining recruitment data.Assess the acceptability of the intervention through qualitative interviews and retention rates during the study.Determine duration of the intervention before transplantation starts by monitoring point of recruitment to the study and time to transplant.Explore the appropriateness of outcome measures/completeness by qualitative interview responses, completion rates, time to complete.

## Methods and analysis

### Methodology

Mixed methods, combining qualitative and quantitative data collection and analysis, are used to achieve the described aims and objectives.

### Design

This is a prospective feasibility study (see figure 1 for study flow chart).

**Figure 1 F1:**
[figure not shown]
Recruitment and intervention flow chart. 6MWD, 6 min walking distance; DVD, digital versatile disc; PROMs, patient-reported outcome measures.

### Setting

Assessments and exercise sessions take place in the physiotherapy outpatient department in an acute hospital trust, which is a regional specialist centre for haematological services. Patient interviews take place in private rooms in the physiotherapy department or over the telephone for patient convenience.

### Feasibility

The feasibility of the intervention is determined through the following targets:Recruitment: based on patient numbers at the study site, the recruitment target is 24 patients in a 12-month period (ie, two patients per month).Attendance: minimum average attendance at exercise sessions of 66% of the scheduled/invited sessions.Retention: 80% patient retention to 6-week follow-up assessment.Adverse events: adverse events are closely monitored and used to inform decisions to proceed.

Acceptability of the intervention to patients is also determined through the qualitative data collection and analysis, described in a later section.

### Quantitative data collection and analysis

Data collection will take place between September 2016 and February 2018.

#### Sampling

Consecutive sampling is used to recruit patients to this study who have a diagnosis of multiple myeloma and have been assigned to the autologous transplantation list. The recruiting centre transplants approximately 70 patients with myeloma per year: sampling all patients over a 12-month period will indicate study recruitment feasibility. This feasibility study did not have a formal sample size calculation to determine a priori the number of participants to recruit; it aimed to recruit for a fixed period of time (12 months) at a single centre, and one of the outcomes was to estimate the recruitment rate per month.

#### Inclusion criteria

All patients with a diagnosis of multiple myeloma, assigned to the autologous transplantation waiting list for either a first or second transplant.^22^

#### Exclusion criteria

To allow safe completion of initial objective assessments, patients with a history of unstable angina or heart attack in the previous month are excluded.^23^ Medical stability is a prerequisite for transplantation, therefore no patients are excluded on this basis.

#### Recruitment

Patients are screened at clinic appointments by the bone marrow transplant team during their preparation for transplant. Patients meeting the inclusion criteria are provided with verbal and written information and invited to be involved in the study. Follow-up takes place after 48 hours via a phone call from a study physiotherapist: any remaining questions are discussed, and if the patient agrees to take part then written consent is obtained and an initial assessment appointment is made.

Patients who choose not to join the study are invited to take part in a qualitative interview to explore their reasoning (figure 1). This is described in more detail under Qualitative data collection and analysis.

#### Intervention

##### Initial assessment

Patients attend an initial assessment with a study physiotherapist who undertakes the following:explanation of the prehabilitation programmedocumentation of written consentsubjective history including comorbidities and patient goalsinduction to the gym area equipmentprovision of booklet and digital versatile disc with physical activity advicebaseline objective assessment (table 1)design of individualised gym programme in line with patient abilities and goalscompletion of an initial gym circuit with close supervision.

##### Weeks 2–5

Patients attend weekly 1-hour physiotherapist-led group gym sessions and complete their individualised programmes. Supervision is available as required and programmes are progressed in line with patient ability and performance.

##### Week 6

Completion of final gym circuit and repeat of objective assessments (table 1).

##### Follow-up

Patients are followed up on admission for transplant, and again on transplant discharge, for further repeat of objective assessments (table 1).

**Table 1 T1:** Study data collection

	Recruitment	Initial assessment	Weeks 2–5	Week 6	Transplant admission	Transplant discharge
Screening data	✓					
Demographic data		✓				
6 min walking distance test		✓		✓	✓	✓
PROMs		✓		✓	✓	✓
Activity data		✓	✓	✓	✓	✓
Adverse events		✓	✓	✓		

PROMs, patient-reported outcome measures.

#### Outcome measures

The following data are captured for study participants.

##### Screening data

Through initial screening and recruitment, data are collected on:number of patients meeting inclusion criteriapatients accepting initial study informationpatients agreeing to attend for initial assessmentreasons for non-participation.

##### Demographic data

The following demographic data are captured during the initial assessment:genderlength of diagnosisbaseline physical activity levelstransplant historypretransplant therapies receivedtime to transplantation from decision to transplantother relevant information.

##### Functional measure

Patients undertake a 6 min walking distance (6MWD) test before and after the exercise intervention. The 6MWD test is a useful field test of functional capacity, is safe to administer and although it has less correlation with peak oxygen capacity than the shuttle walk test, it is better tolerated by patients and is more reflective of activities of daily living as it is a submaximal exercise test.^23^ The 6MWD test has been found to be a valid and reliable test in patients with cancer.^24^

##### Patient reported outcome measures

As this is a feasibility study, it is useful to determine the feasibility and acceptability of outcomes to be used. For this reason, two different sets of patient reported outcome measures (PROMs) are issued to alternate patients taking part in the study (table 2). The data collected in the outcome measures and in the qualitative interviews will determine their value in any future studies.

**Table 2 T2:** Patient reported outcome measures

Group	Category	Measure
Physical activity/fitness	Group 1	International Physical Activity Questionnaire^25^
	Group 2	Godin Leisure Time^26^
Mental well-being	Groups 1 and 2	Warwick and Edinburgh Mental Well-being Scale^27^
Quality of Life	Group 1	Functional Assessment of Cancer Therapy - Multiple Myeloma (FACT-MM)^28^
	Group 2	European Organisation of Cancer Treatment Quality of Life Questionnaire (EORTC QLQ)^29^
Self-efficacy for exercise	Groups 1 and 2	Self-Efficacy for Exercise Scale^30^

##### Activity data

The following activity data are collected for each participant:the number of gym attendancesfollow-up compliancewithdrawals from the study and at which stage of the study these occurreasons for withdrawal or non-attendance.

##### Data collection

Table 1 shows the full data collection schedule for the study.

#### Data analysis

Flow of participants through the study is captured, and the baseline clinical and demographic characteristics of consented participants assessed with appropriate summary statistics.

The data analysis for the feasibility objectives uses descriptive statistics and focuses on CI estimation.The feasibility of recruitment to main trial is assessed with the consent rate (defined as the ratio of number of consented participants/number of eligible participants) and its associated 95% CI, and the recruitment rate per month and its associated 95% CI. The target recruitment rate is a minimum of two participants per month.Reporting of the number and characteristics of eligible patients approached for the study and reasons for refused consentReporting of study participant retention rates at 6-week follow-up (eg, participants with a valid 6MWD outcome— the probable primary outcome for the main trial) and its associated 95% CI. The target is a minimum of 80% retention to 6-week follow-up assessment.Reporting of the number (and rate) of serious adverse events/incidents (and its associated 95% CI) experienced by the participants in the pretransplantation period. A serious adverse event (SAE) is defined as any adverse event or adverse reaction that results in death, is life-threatening, requires hospitalisation or prolongation of existing hospitalisation, results in persistent or significant disability or incapacity, or is a congenital anomaly or birth defect.Reporting of the decision on primary endpoint for any main trial (current estimate suggests 80% power, two-sided, with n=610 to detect 5% (18 metre) difference in 6MWD test with 10% dropout at 12 metre).

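### The consent and monthly recruitment rates measure uptake of an exercise programme offered to every participant, yet the plan reads them as feasibility of recruitment to a randomised trial

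*Protocol article*

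**What the plan says.** The Aims and objectives section of the protocol article states the aim: to "determine whether it is feasible to conduct a randomised controlled trial into pretransplant exercise". The Design section says: "This is a prospective feasibility study". The abstract says that the study identifies patients on the transplant list and "invites them to participate in six weekly sessions of individualised, supervised exercise while awaiting transplantation". The Intervention section describes one pathway for all: initial assessment, weekly gym sessions, a repeat assessment at week 6. The only division of participants concerns questionnaires: "two different sets of patient reported outcome measures (PROMs) are issued to alternate patients taking part in the study".

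The Data analysis section then states: "The feasibility of recruitment to main trial is assessed with the consent rate". It defines that rate as the "ratio of number of consented participants/number of eligible participants" and adds the monthly recruitment rate, each with a 95% CI, against a minimum of two per month. It also sets a minimum of 80% retention at the 6-week assessment.

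On non-participants, the Recruitment section says: "Patients who choose not to join the study are invited to take part in a qualitative interview to explore their reasoning". The interview topics in the qualitative section cover non-participation, experience of the intervention, matters relevant to a future design such as recruitment and attendance, and barriers and enablers. Neither randomisation nor a control arm is named there.

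**The concern.** A patient who consents here accepts a supervised exercise programme that they are certain to be offered. A patient who consents to a randomised trial accepts that chance will decide whether they get it. These are different decisions, and the rate for one need not equal the rate for the other. The plan observes the first and, in its own wording, uses it to assess the second.

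At stake is the conclusion the study exists to reach. The Discussion says that confirmed feasibility leads to a larger efficacy study. The planned 95% CIs do not protect against the mismatch, because they describe sampling error in uptake of the programme, not the change of question. Retention raises the same issue: 80% at week 6 among patients who are all exercising says nothing directly about patients allocated to a control.

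**Working it through.** **Step 1: the plan's own figure.** The Feasibility section gives a target of 24 patients in 12 months. 24 / 12 = 2.0 per month, as stated.

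**Step 2: what the planned interval covers.** If exactly 24 are recruited, the exact Poisson 95% CI for the monthly rate has lower limit χ²(0.025; 48) / 2 / 12 = 1.28 and upper limit χ²(0.975; 50) / 2 / 12 = 2.98. Against the roughly 70 myeloma transplants a year given under Sampling, 24 / 70 = 34.3% (Wilson 95% CI 24.2% to 46.0%). The 70 is only a stand-in for the consent rate's real denominator, which is eligible patients. Both intervals concern uptake of the offered programme.

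**Step 3: where randomisation might be measured.** Going through the protocol article section by section:

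- Aims and objectives: the eight objectives cover acceptability of study and intervention, reasons for non-consent, existence of a cohort, recruitment point, eligibility criteria, duration and outcome measures. None covers randomisation.
- Feasibility: the targets are recruitment, attendance, retention and adverse events. None covers a control arm.
- Screening data: counts of patients meeting the criteria, accepting information and agreeing to assessment, plus reasons for not taking part. No item on randomisation.
- Activity data: attendance, follow-up compliance and withdrawals, all within the exercise programme.
- Qualitative section: the listed topics do not name randomisation or a control arm, but the list is illustrative and the guide is described as flexible.
- Strengths and limitations: the limit stated on inference concerns effectiveness. Transfer of the consent rate to a randomised trial is not mentioned.

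**Step 4: can the gap be sized or signed?** Let w be the share of consenters who would also accept randomisation, and v the share of decliners who would accept it. Taking 70 eligible patients for illustration, 24 consent and 70 − 24 = 46 decline. The yearly number for a randomised trial is then 24w + 46v. The documents give neither w nor v, so every value below is an assumption.

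| w | v | Yearly number | Per month |
|---|---|---|---|
| 1.0 | 0 | 24.0 | 2.0 |
| 0.8 | 0 | 19.2 | 1.6 |
| 0.6 | 0 | 14.4 | 1.2 |
| 0.6 | 0.2 | 14.4 + 9.2 = 23.6 | 2.0 |
| 0.8 | 0.2 | 19.2 + 9.2 = 28.4 | 2.4 |

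The two effects cancel when v = 24(1 − w) / 46. For w = 0.8 this is 4.8 / 46 = 10.4%; for w = 0.6 it is 9.6 / 46 = 20.9%. A modest share of decliners willing to be randomised would offset a sizeable refusal among consenters, so the sign of the difference is open.

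**The case against.** A non-randomised feasibility stage before a randomised trial is a legitimate choice, and nothing here says that this study should have randomised. The recruitment rate is also not a sole go/no-go rule: the Feasibility section adds attendance, retention, adverse events and qualitative acceptability, and introduces its targets as tests of the intervention. Both points stand. They do not remove the sentence in Data analysis that ties main-trial recruitment to this study's rates.

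The interviews might cover the gap. The topic list is open-ended, the guide adapts as the study proceeds, and the guide itself is not shown. This also stands, so a reader should not infer that the question is certain to go unasked. What can be said is that it is not measured quantitatively and not named among the listed topics.

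A reader might also infer that the consent rate must overstate recruitment to a randomised trial, because patients keen to exercise would refuse a control arm. The documents do not support that. The Discussion expects time commitments, wellness and enjoyment of exercise to affect feasibility, and a patient who declines a certain weekly commitment might accept a chance of not having it. Nor is the long recruitment time implied by the main-trial estimate a measure of this problem: 610 / 2 = 305 centre-months arises with no refusal of randomisation at all.

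Finally, the main-trial comparator is not defined in the article, and willingness to be randomised depends on it. This bears on how the remedy is worded, not on whether the mismatch exists.

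**Conclusion.** The point holds as a mismatch between what is measured and what is concluded. The consent and monthly rates estimate uptake of a programme offered to everyone. The plan uses them to assess recruitment to a randomised trial, and neither the quantitative measures nor the named interview topics supply the missing link. No stated figure is wrong. Neither the direction nor the size of any difference can be known from the documents; the illustrations, from 1.2 to 2.4 per month, rest wholly on assumed willingness and on 70 as the number eligible. The reading that the study is single-arm follows from the described pathway and is not the article's own term. The change should be made: followed as written, the plan would draw a conclusion about randomised recruitment that its data cannot support alone.

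**What to change.** In Data analysis, describe the consent and monthly rates as uptake of the offered exercise programme, and the 80% target as retention among patients receiving exercise. State that neither alone establishes recruitment or retention in a randomised trial. This costs only wording and can be done even if recruitment has ended.

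In addition, ask one fixed question: would the patient join a trial in which chance decided between the programme and the comparator envisaged for the main trial? The sponsor must name that comparator first. Ask only after the patient has decided about this study: after consent for participants, and when the decision is recorded or at interview for decliners. Asked earlier, for instance at the 48-hour call before written consent, it could suggest that this study randomises.

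Report the proportion willing among those asked, with its 95% CI and the number not asked, beside the consent rate as supporting evidence. Dividing by all eligible patients would count everyone not asked as a refusal. Add acceptability of randomisation and of a control arm to the interview topics.

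The cost is one question and a topic-guide line. A hypothetical answer is only a proxy for behaviour, and because the study is under way, patients already enrolled would lack the item unless asked later.

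### SAEs are to be reported for the pretransplantation period, but adverse-event collection is scheduled only to week 6

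*Protocol article*

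**What the plan says.** Two parts of the protocol article bear directly on the point.

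- **Reporting.** The Data analysis section plans "Reporting of the number (and rate) of serious adverse events/incidents (and its associated 95% CI) experienced by the participants in the pretransplantation period".
- **Collection.** The row "Adverse events" in Table 1 (under Follow-up) has ticks at initial assessment, weeks 2–5 and week 6, and none at recruitment, transplant admission or transplant discharge. The Data collection section states: "Table 1 shows the full data collection schedule for the study".

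Three other parts set the context. The Follow-up section provides assessments at transplant admission and at discharge, as time points separate from week 6. Table 1 schedules the walking test, the patient-reported measures and activity data at both. The Feasibility section lists adverse events beside recruitment, attendance and retention, and says that "adverse events are closely monitored and used to inform decisions to proceed". The strengths and limitations box says of the data-collection time points, which follow clinical care: "They are therefore subject to variations, and not within the control of the study team".

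**The concern.** The period named for reporting naturally ends at transplant, while the period scheduled for collection ends at week 6. A participant who is admitted some weeks after finishing the programme passes through an interval that the reported figure claims to cover and that no scheduled collection point covers.

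The error can go only one way. Uncollected events lower a count, and they lower a per-participant proportion and its upper confidence limit. The figure is one of the inputs to the judgement on whether to proceed to a main trial. A reader who takes the label at face value would believe that safety had been observed up to transplant when it had been observed for the programme weeks only.

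**Working it through.** The article states no SAE rate, SAE precision or SAE sample size, so there is no figure to reproduce. The check is one of consistency, followed by an illustration of size.

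**1. Does collection end before the reporting period does?** Table 1 has separate columns for week 6 and for transplant admission. The adverse-event row is blank at admission, while three other rows are ticked there. Because the table is described as the full schedule, a blank means not scheduled. No other section schedules adverse-event collection between week 6 and admission.

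**2. Could the reporting label simply mean the six-week programme?** The article does not define it that way. The retention item in the same Data analysis list is tied explicitly to the 6-week follow-up, so that window is named where it is meant.

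**3. Do other data fill the gap?** Activity data are collected at admission, but the Activity data section limits them to attendances, follow-up compliance, withdrawals and reasons for withdrawal or non-attendance. They might reveal some SAEs incidentally. An SAE without withdrawal or non-attendance would not appear.

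**4. How large is the gap?** Let W be the weeks from initial assessment to transplant admission. No value is given, and learning about this timing is a study objective: "Determine duration of the intervention before transplantation starts by monitoring point of recruitment to the study and time to transplant". W is therefore an assumption here. Taking scheduled collection as six weeks:

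share of the wait covered = 6 / W, for W of 6 or more.

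For illustration, take the recruitment target of 24 participants and an assumed constant 0.01 SAEs per participant-week:

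- expected SAEs to week 6 = 24 × 0.01 × 6 = 1.44
- expected SAEs to admission = 24 × 0.01 × W

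| W (weeks, assumed) | Share covered | Expected SAEs to week 6 | Expected SAEs to admission |
|---|---|---|---|
| 6 | 6/6 = 100% | 1.44 | 1.44 |
| 8 | 6/8 = 75% | 1.44 | 1.92 |
| 12 | 6/12 = 50% | 1.44 | 2.88 |

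**5. Does the form of the rate matter?** Yes, and the article does not fix the denominator.

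- Count or per-participant proportion labelled as pretransplantation: too low whenever W exceeds 6 and events occur after week 6.
- Person-time rate with both windows ending at week 6: 1.44 / (24 × 6) = 0.010 per participant-week. This is correct for those weeks, and only the label is too wide.
- Person-time rate with events to week 6 and a denominator to admission at W = 12: 1.44 / (24 × 12) = 0.005 per participant-week, half the assumed true rate.

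**The case against.** The strongest reply is that this may be no more than a loose label. With no denominator defined, a six-week count over six-week person-time is unbiased for the weeks observed. The outcome is descriptive: the Feasibility section sets numerical targets for recruitment, attendance and retention but none for adverse events, so no threshold would be crossed because of the label. SAEs caused by exercise would also plausibly cluster in the supervised weeks, which are covered. All of this stands and limits the weight of the point. It does not remove the disagreement between a stated reporting period and a stated schedule. That is not a detail which the article merely leaves to a fuller protocol.

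Two stronger readings are tempting, and the document does not support them.

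- A reader might infer that a large share of SAEs must be missed, because the Rationale says that "usually a period of 4–6 months exists to offer prehabilitation between diagnosis or relapse and the commencement of the autologous stem-cell transplantation process". That window starts at diagnosis or relapse, whereas participants join once they are on the transplant list. The time from joining to admission may be much shorter, and the share missed would in any case depend on an assumed constant event rate.
- A reader might infer that non-serious events are left out of the analysis, because only SAEs are named in the Data analysis section. Tabulations of other adverse events are commonly left to a full protocol or analysis plan, neither of which is shown. The Feasibility section refers to adverse events generally.

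**Conclusion.** The inconsistency is real. SAEs are to be reported for the pretransplantation period, while adverse-event collection is scheduled only to week 6 and admission is a later, separate assessment. For participants admitted after week 6, a count or per-participant proportion under that label would be understated. A person-time rate would be understated only if its denominator ran to admission.

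The size cannot be derived from the article. It is zero if every participant is admitted by week 6. On assumed waits of 8 and 12 weeks, collection covers 75% and 50% of the period. The conclusion rests on Table 1 being complete, as the article says it is, and on the ordinary meaning of the pretransplantation period as the time up to transplant. The consequence is a safety statement wider than its data. It is not a demonstrated wrong decision, since no SAE threshold is set.

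**What to change.** Make Table 1 and the Data analysis section agree, in one of two ways.

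1. **Extend collection.** Add adverse events to the transplant-admission column of Table 1, asking about events since week 6. A question at that visit will not reach everyone: the plan's own target is 80% retention at week 6, and it tracks withdrawals. SAE status should therefore also be checked, for example from hospital records, for participants who withdraw, die or do not reach transplant. State the denominator and let the event window and the denominator window end at the same point.
2. **Relabel.** Keep the schedule and describe the result as SAEs during the 6-week programme.

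The first costs one more question at an existing visit and a records check. The second costs a few words and gives a narrower safety statement.
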